## TRIAL SUMMARY

|                                       |                                                                                                              |                                                                                                                                                                                                                                                      |
|---------------------------------------|--------------------------------------------------------------------------------------------------------------|------------------------------------------------------------------------------------------------------------------------------------------------------------------------------------------------------------------------------------------------------|
| Trial Title                           | RECOVERY-RS Respiratory Support: Respiratory Strategies in COVID-19; CPAP, High-flow, and standard care      |                                                                                                                                                                                                                                                      |
| Internal ref. number (or short title) | RECOVERY-Respiratory Support                                                                                 |                                                                                                                                                                                                                                                      |
| Clinical Phase                        | Phase III                                                                                                    |                                                                                                                                                                                                                                                      |
| Trial Design                          | Adaptive (group-sequential), pragmatic, randomised controlled, open-label, multi-centre, effectiveness trial |                                                                                                                                                                                                                                                      |
| Trial Participants                    | Adult, critically ill patients, with suspected or confirmed, COVID-19                                        |                                                                                                                                                                                                                                                      |
| Planned sample size                   | 4002                                                                                                         |                                                                                                                                                                                                                                                      |
| Treatment Duration                    | 30 days                                                                                                      |                                                                                                                                                                                                                                                      |
| Follow-up Duration                    | 30 days or hospital discharge, whichever comes latest                                                        |                                                                                                                                                                                                                                                      |
| Planned Trial Period                  | 18 months                                                                                                    |                                                                                                                                                                                                                                                      |
|                                       | Objectives                                                                                                   | Outcome Measures                                                                                                                                                                                                                                     |
| Primary                               | To determine if CPAP or HFNO is clinically effective compared to standard care (excluding CPAP or HFNO)      | Intubation and mortality                                                                                                                                                                                                                             |
| Secondary                             | To assess in-hospital patient data in terms of their stay                                                    | Intubation rates; time to intubation; time to death (mortality); mortality in critical care (Level 2/3); mortality in hospital stay; mortality at 30 days; admission to ICU; length of stay in critical care (Level 2/3); length of stay in hospital |

## LIST OF ABBREVIATIONS/GLOSSARY

| Abbreviation | Explanation                                               |
|--------------|-----------------------------------------------------------|
| AE           | Adverse event                                             |
| ARF          | Acute respiratory failure                                 |
| BiPAP        | Bilevel positive airway pressure (BiPAP)                  |
| CI           | Chief Investigator                                        |
| CONSORT      | Consolidated Standards of Reporting Trials         |
| COVID-19     | Coronavirus Disease 2019                                  |
| CPAP         | Continuous positive airway pressure                       |
| CRF          | Case Report Form                                          |
| CTU          | Clinical Trials Unit                                      |
| DMC          | Data Monitoring Committee                                 |
| GCP          | Good Clinical Practice                                    |
| HFNO         | High flow nasal oxygen                                    |
| ICF          | Informed Consent Form                                     |
| ICNARC       | Intensive Care National Audit and Research Centre         |
| ICU          | Intensive Care Unit                                       |
| IRAS         | Integrated Research Application System                    |
| ISRCTN       | International Standard Randomised Controlled Trial Number |
| MRC          | Medical Research Council                                  |
| NIV          | Non-invasive ventilation                                  |
| NNT          | Number needed to treat                                    |
| PI           | Principal Investigator                                    |
| PPI          | Patient & Public Involvement                              |
| RCT          | Randomised Controlled Trial                               |
| REC          | Research Ethics Committee                                 |
| R&D          | Research and Development                                  |
| SAE          | Serious Adverse Event                                     |
| SARS-CoV-2   | Severe acute respiratory syndrome coronavirus 2           |
| SOP          | Standard Operating Procedure                              |
| TSC          | Trial Steering Committee                                  |
| WCTU         | Warwick Clinical Trials Unit                              |

# **1. BACKGROUND**

## **1.1 Epidemiology and burden of the condition**

Severe acute respiratory syndrome coronavirus 2 (SARS-CoV-2) emerged at the end of 2019 as a novel coronavirus, resulting in a current global pandemic of respiratory illness, Coronavirus Disease 2019 (COVID-19). Using very recent World Health Organization (WHO) data on the cumulative number of deaths up to 1 March 2020, mortality rates of 5.6% (95% CI: 5.4%–5.8%) for China and 15.2% (12.5%–17.9%) outside of China have been reported. Indeed, as of 29 March 2020, there have been 575,444 confirmed cases, with 26,654 confirmed deaths, across 202 countries (available at <https://www.who.int/emergencies/diseases/novel-coronavirus-2019>). National statistics detailed by the Centre of Evidence Based Medicine, University of Oxford, report all-cause mortality by respiratory disease, across England and Wales, during 3 January 2020 to 13 March (i.e. during the COVID-19 outbreak) have averaged approximately 15%, albeit peak pandemic phase has not yet occurred in the UK. A recent (27 March 2020) report from the Intensive Care National Audit and Research Centre (ICNARC), reported 846 admissions to critical care units in England, Wales, and Northern Ireland with confirmed COVID-19; where 24 hour outcome data were available in 775 patients, 79 had died, 86 were discharged alive, and 609 patients remained in critical care.

COVID-19 has a wide spectrum of clinical severity, ranging from asymptomatic to critically ill, and ultimately death. A common and prominent complication of advanced COVID-19 is acute hypoxemic respiratory insufficiency requiring oxygen and ventilation therapies. Often deterioration may be rapid. A recent report showed that 14% of patients developed dyspnea, tachypnea with a respiratory rate greater than or equal to 30 per minute, desaturation with peripheral oxygen saturation (SpO2) less than or equal to 93%, poor oxygenation with a ratio of partial pressure of arterial oxygen (PaO2) to fraction of inspired oxygen (FiO2) less than 300 mmHg, or lung infiltrates greater than 50%, within 48 h.

Ventilatory support is the cornerstone of management for COVID-19 patients presenting with respiratory impairment. Reports from China, the source of the pandemic, suggest a prevalence of hypoxic respiratory failure in patients with COVID-19 of 19%, although true global figures are unclear. That said, there is evidence that patients have received as standard care management in the form of supplemental oxygen therapy, high-flow nasal oxygen (HFNO), continuous positive airways pressure (CPAP), non-invasive positive pressure ventilation (NIV), and invasive mechanical ventilation. Standard care treatment for patients requiring ventilatory support may involve more than one method and a cross over between non-invasive and invasive devices.

Already the potential impact of the respiratory symptomology associated with COVID-19 on UK critical care units can be appreciated; nearly 80% of the patients in the aforementioned ICNARC report required invasive mechanical ventilation, compared with just over 40% in a non-COVID-19 cohort of viral pneumonia between 2017-2019. However the ability to deliver this treatment at this scale (and potentially greater) across UK critical care settings places huge pressures on existing services with finite resources. This scenario of excess demand on limited ventilator availability and critical care bed capacity is currently being witnessed worldwide, in particular in neighbouring European countries.

Determining the most effective form of ventilatory support for patients with COVID-19 is therefore paramount to ensure optimum therapy is delivered to patients, and to protect UK vital critical care resources and infrastructure. Findings from this trial will also have the potential to inform global ventilation practice for patients with COVID-19.

## **1.2 Existing knowledge**

### **High flow nasal oxygen**

There is currently no direct evidence to support the use of HFNO in patients with COVID-19; instead evidence around the possible application of this therapy in COVID-19 is derived from the acute respiratory failure (ARF) population where it appears inconsistent overall. The most recent relevant Cochrane systematic review and meta-analysis from 2017 demonstrated that the evidence to support the use of HFNO for acute respiratory failure was insufficient to conclude, whether HFNO provided safe and effective respiratory support to these patients. The majority of trials (10 out of 11) included in this review compared HFNC versus low-flow oxygen. This review was unable to demonstrate whether HFNO was more effective or safe than other oxygen delivery devices. For the primary outcomes of treatment failure, defined as need for non-invasive or invasive ventilation (1066 participants; six studies) and mortality (755 participants; three studies), investigators found no differences between HFNO and low-flow oxygen therapies (risk ratio (RR), Mantel-Haenszel (MH), random-effects 0.79, 95% confidence interval (CI) 0.49 to 1.27; and RR, MH, random-effects 0.63, 95% CI 0.38 to 1.06, respectively). There was no evidence that HFNO reduced the rate of treatment failure or risk of death compared with low-flow oxygen devices, and also no evidence of any advantage for HFNO in terms of adverse event rates, ICU length of stay, or duration of respiratory support. In this review the data comparing HFNO to CPAP or Bilevel positive airway pressure (BiPAP) was very limited.

In another recent systematic review and meta-analysis comparing HFNO with usual care, there was no difference in mortality (HFNO, 60/1,006 [6%] vs usual care, 90/1,106 [8.1%]) (n = 2,112; p = 0.29;

I2, 25%; fixed effect model: odds ratio, 0.83; 95% CI, 0.58–1.17) or rate of intubation (HFNC, 119/1,207 [9.9%] vs usual care, 204/1,300 [15.7%]) (n = 2,507; p = 0.08; I2, 53%; random effect model: odds ratio, 0.63; 95% CI, 0.37–1.06). A qualitative analysis of 13 studies on tolerability and comfort suggested that HFNO was associated with improved patient comfort and dyspnea scores. In contrast, other recent systematic reviews and meta-analyses have demonstrated a benefit of HFNO in reducing intubation compared with conventional oxygen (RR 0.85, 95% CI 0.74 to 0.99), but similarly no effect on risk of death or ICU length of stay. Reducing the need for intubation is a clinically meaningful outcome, with additional important benefits for healthcare resource utilisation.

Current Surviving Sepsis Campaign (SSC) COVID-19 guidelines make a weak recommendation, based on low quality evidence, for using HFNO over conventional oxygen therapy. A similar strength of recommendation is made for using HFNO over NIV, based on contrasting evidence around the effectiveness for HFNO to reduce mortality, need for intubation, and ICU length of stay and potential for greater patient tolerability for HFNO. Guidelines from the Australia and New Zealand Intensive Care Society (ANZICS) similarly recommend HFNO for patients presenting with hypoxia. Both sets of guidelines do however, advise close monitoring of patients receiving either HFNO in a setting of sufficient acuity to enable controlled intubation in the event of deterioration given the high risk of failure.

### **Continuous positive airway pressure**

There are currently no data available on the use of CPAP directly in patients with COVID-19. A number of trials have explored the effectiveness of CPAP in ARF. These trials provide some evidence that CPAP has a role in improving important outcomes such as progression to intubation, length of stay in ICU and/or hospital. In a 2015 Cochrane systematic review and meta-analysis, Faria *et al* compared the effectiveness of NIV i.e. continuous positive airway pressure (CPAP) or bi-level NIV, in reducing mortality and the rate of tracheal intubation in adults with acute respiratory failure after upper abdominal surgery, compared to standard therapy (oxygen therapy). Two trials involving 269 participants were included and CPAP or bi-level NIV reduced the rate of tracheal intubation (risk ratio (RR) 0.25; 95% confidence interval (CI) 0.08 to 0.83 with a number needed to treat (NNT) for additional benefit of 11. There was very low quality evidence that the intervention may also reduce ICU length of stay (mean difference (MD) -1.84 days; 95% CI -3.53 to -0.15) however there were no differences for mortality (low quality evidence) and hospital length of stay.

Bakke *et al* explored the effectiveness of CPAP and NIV versus standard medical treatment in prehospital treatment of patients with acute respiratory failure in terms of mortality, hospital

length of stay, intensive care unit length of stay or intubation rate. Four studies in this review were high quality studies comparing CPAP to standard care, with only 1 trial showing a reduction in both mortality and intubation rate. The remaining 3 high quality studies showed no significant differences in any of the outcomes of interest albeit showing a trend toward lower intubation rate with supplementary CPAP. Four studies in this review compared NIV to standard medical treatment, and found no difference in mortality or intubation rate, and two studies demonstrated a reduction in ICU stay. Williams *et al* included studies comparing CPAP (and usual care) with no CPAP for ARF in the prehospital setting; a meta-analysis included 5 studies (3 RCTs, 1 non-randomised comparative study, and 1 retrospective comparative study) totalling 1002 patients and showed pooled estimates demonstrated significantly fewer intubations ([OR] 0.31; 95% confidence interval [CI] 0.19-0.51) and lower mortality (OR 0.41; 95% CI 0.19-0.87) in the CPAP group.

Current international guidelines do not address the use of CPAP in COVID-19 patients, focusing instead on HFNO, NIV, and invasive mechanical ventilation once patients are intubated. In contrast, national guidance from NHS England state that CPAP is the preferred form of non-invasive ventilator support; HFNO is not advocated due to lack of efficacy.

### **Non-invasive ventilation**

There is no direct evidence to support the use of NIV in patients with hypoxic respiratory failure, with some reports of increased risk to healthcare workers of exposure to infection. Previous meta-analyses where reductions in intubation and mortality have been demonstrated with NIV have been in patient populations less relevant to COVID-19. Failure rates are generally high with use of NIV outside of cardiogenic pulmonary oedema. Should other pathophysiology be present e.g. acute hypercapnic respiratory failure, NIV may be considered. Surviving Sepsis Campaign guidelines recommend HFNO over NIV, based on contrasting evidence around the effectiveness for HFNO to reduce mortality, need for intubation, and ICU length of stay and potential for greater patient tolerability for HFNO. In patients with COVID-19, where HFNO is not available and there is no urgent need for intubation, a trial of NIV with close monitoring and short-interval assessment for deterioration may be considered (weak recommendation, very low quality evidence).

## **1.3 Hypothesis**

In adult patients, with suspected or confirmed COVID-19, CPAP or HFNO are more effective than standard care for reducing the rate of intubation and / or mortality.

We will aim to recruit a maximum of 4002 patients to explore this hypothesis. However, as this is an adaptive trial (group-sequential) in design, we will review the data at each stage using formal

interim analyses and continue with all arms or drop an intervention arm if required. The trial will therefore stop early and not require this total sample size if an intervention appears to be effective at an interim analysis.

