In our sample size calculation, we have assessed both outcome measures and taken the largest in terms of the incidence, to ensure we have maximum power and sample size for our study. Therefore taking the data from Baud *et al* to be representative of usual care and assuming a conservative incidence of 15% for the composite outcome of intubation or mortality on the usual care arm, then using a two-sided 5% significance level, a total 3000 patients (1000 per arm across 3 arms) would give approximately 90% power to detect an odds ratio of 0.625, corresponding to a reduction from 15% to 10% in the composite event rate. allowing for the 11 interim analyses. Our comparisons will be based on CPAP versus standard care and HFNO versus standard care and allow for the formal interim analyses as agreed with the DMC.

However, there remain many uncertainties regards the sample size parameters and also whether an equal randomisation allocation ratio will be maintained. For this reason we have inflated our sample size to 4000 patients (4002 across the three arms) to maintain the study power and detect small effect sizes, if they exist. It may allow us to also assess the difference between CPAP and HFNO, if difference between these interventions are small enough to be detected with this larger sample size. Furthermore, it may be likely that we will not need all these patients if the trial stops at a formal interim analysis or if the DMC recommends that an arm is dropped.

The formal stopping rules will be set out in the statistical analysis plan, following discussions with the DMC. These criteria will be used to accept or drop an intervention arm, based on the assessment of the primary outcome at each interim point.

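### Section 1.3 stops the whole trial when one device appears effective, which does not fit the two separately powered comparisons of section 6.1

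*Protocol*

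**What the plan says.** Section 1.3 gives a maximum of 4002 patients and says that interim analyses may lead to all arms continuing or to one being dropped. It then adds: "The trial will therefore stop early and not require this total sample size if an intervention appears to be effective at an interim analysis". The subject is the trial, and the trigger is one of two interventions.

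Section 6.1 works per comparison: "Our comparisons will be based on CPAP versus standard care and HFNO versus standard care". Its power statement is that "a total 3000 patients (1000 per arm across 3 arms) would give approximately 90% power to detect an odds ratio of 0.625", which it says allows for 11 interim analyses. It leaves the formal stopping rules to the SAP but says what they will do: "These criteria will be used to accept or drop an intervention arm". It also names the trial stopping and an arm being dropped as two different events.

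Section 2.2 gives harm or ineffectiveness as the reasons for dropping one intervention. Section 2.12 lists three grounds for premature stopping: the Ethics Committee, a DMC recommendation, and loss of funding. Section 7.10 has the DMC receive outcome reports at four time points and make recommendations to the TSC. No section says what happens to the other device's comparison after one device has succeeded.

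**The concern.** The power in 6.1 belongs to a comparison that runs until it crosses its own boundary or reaches its full size. Read as written, 1.3 removes that condition. As soon as one device crosses, the other comparison ends with whatever data it has, even if that device works equally well.

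The trial has two primary comparisons, and section 1.4 puts weight on the relative effectiveness of the options and on the preferred mode of support. A trial that stops with one device shown and the other unresolved answers only half of that. It would also answer it with less power than the protocol states.

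**Working it through.** **Inputs.** From 6.1: test "using a two-sided 5% significance level"; control rate, "assuming a conservative incidence of 15% for the composite outcome of intubation or mortality on the usual care arm"; effect, "corresponding to a reduction from 15% to 10% in the composite event rate"; 1000 per arm; 11 interim analyses, so 12 looks. The maximum of 1334 per arm is also from 6.1. Four looks come from 7.10; both look counts were run because the two sections differ.

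**Assumptions not in the protocol.** Boundary shape; equally spaced looks (the list of tables mentions four equally spaced looks); equal allocation; a complete 30-day outcome for every patient counted at a look.

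**Step 1. Reproduce the stated power.** With p1 = 0.15, p2 = 0.10, mean 0.125 and n = 1000:

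power = Φ[(0.05 − 1.96 × √(2 × 0.125 × 0.875/1000)) / √((0.1275 + 0.0900)/1000)]

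= Φ[(0.05 − 1.96 × 0.01479) / 0.01475] = Φ(1.42) = 92.3%.

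This is the fixed-sample figure; 90% needs 918 per arm. With 12 looks, simulated power for one comparison is 91.6% with O'Brien-Fleming-type spending and 86.0% with Pocock-type spending. The stated figure of about 90% is therefore sound for one comparison run to its own end under an O'Brien-Fleming-type boundary.

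**Step 2. Apply the rule of 1.3 when both devices are at 10%.** A device is now shown to work only if it crosses first or at the same look as the other. Let A be the chance that at least one crosses (the same under either rule) and S the chance that both cross first at the same look. The two devices are interchangeable here, so

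power per device = (A + S)/2, where A = (sum of the two separate powers) − P(both shown when run separately).

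For 1000 per arm, 12 looks, O'Brien-Fleming-type spending: A = 0.916 + 0.915 − 0.857 = 0.974; S = 0.197; power = (0.974 + 0.197)/2 = 0.586. The direct simulation (100,000 trials, shared control) gives 0.585 and 0.587.

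**Step 3. All designs.** Power per device (%), comparisons run separately → trial stopped at first success:

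| Design | Classical O'Brien-Fleming | O'Brien-Fleming-type spending | Pocock-type spending |
|---|---|---|---|
| 1000 per arm, 12 looks | 91.5 → 58.2 | 91.6 → 58.6 | 86 → 55 |
| 1000 per arm, 4 looks | 91.9 → 70.4 | 92.1 → 70.7 | 88 → 65 |
| 1334 per arm, 4 looks | 97.3 → 75.3 | 97.4 → 75.5 | 95 → 71 |
| 1334 per arm, 12 looks | 97.2 → 61.1 | 97.1 → 61.4 | 95 → 59 |

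With O'Brien-Fleming-type spending, the chance of showing both devices falls from 85.7% to 19.7% (1000 per arm, 12 looks) and from 95.2% to 51.6% (1334 per arm, 4 looks). The share of trials that stop before the last look with exactly one of two effective devices shown is 0.953 × 0.799 = 76% in the first design and 0.942 × 0.491 = 46% in the second.

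**Step 4. Only one device works** (the other stays at 15%). Power for the effective device, run separately against stopped at first success, differs by at most 0.1 point at 1000 per arm: about 91% both ways with 12 looks and 91.9% both ways with 4. At 1334 per arm it is 97% both ways. There is no loss.

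**Step 5. One device better than planned.** If one device is at 7.5% (an assumed value) and the other at 10%, power for the second under the rule of 1.3 is 16–24% with 12 looks and 35–43% with 4. The size of the loss thus depends heavily on the scenario.

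**The case against.** The sentence in 1.3 closes a background section. The formal rules are left to the SAP, 6.1 already speaks of accepting or dropping an arm, and 2.12 makes early stopping depend on a DMC recommendation. The hypothesis and primary objective are worded as CPAP or HFNO, and once one device beats standard care it is ethically contestable to keep randomising to standard care. The chance of showing at least one effective device stays high: 97% at 1000 per arm and 99% at 1334 with O'Brien-Fleming boundaries. Patients still within their 30-day follow-up at a look would later add data to the second comparison, which the simulation does not count.

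Much of this stands. A reader might infer that the trial halts automatically at the first crossing; 2.12 and 7.10 do not support that, since the DMC recommends and the TSC considers. A reader might also infer that the 90% is wrong, or that one range such as 58–75% should replace it. Neither follows: the 90% reproduces, there is no loss when one device works, and that range mixes designs with different starting power. Nor does the protocol say that an unfinished comparison would be reported as negative.

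What does not stand is that the SAP alone settles the matter. Missing boundaries are not the complaint. Section 1.3 already states a consequence, and an arm-level rule in the SAP would contradict it.

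**Conclusion.** The point holds as an inconsistency that bears on what the trial can conclude. Section 1.3 describes a trial-wide stop on one success; 6.1 powers two comparisons and describes arm-level decisions. If 1.3 is followed and both devices have the design effect, power per device at the design to which the 90% refers drops by about 33 points (91% to 58%) under O'Brien-Fleming boundaries, and by about 31 points with Pocock-type spending. With four looks the drop is about 22 points under O'Brien-Fleming boundaries.

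The direction does not depend on boundary shape or number of looks; the size depends on both, and on equal spacing and complete outcome data at each look. The loss is conditional on both devices working. Stopping at first success can be a legitimate choice, but then the stated power needs its condition attached.

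**What to change.** Reconcile 1.3, 2.12 and 6.1. The preferred text would state that efficacy boundaries apply separately to CPAP against standard care and to HFNO against standard care; that crossing one ends that comparison only; and that the DMC then advises, and the TSC decides, whether and how the remaining comparison continues within the 4002 maximum.

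If the sponsor does intend to stop the trial at the first success, keep the rule and change 6.1. Say that the power of about 90% holds for a comparison that runs to its own boundary. Give the lower per-comparison power when both devices work, computed under the actual SAP boundaries and look schedule. Say that an unfinished comparison will be reported as inconclusive.

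The cost is about one paragraph in the protocol and matching SAP text. Under the preferred text the trial may run longer for the second device, though not beyond the existing maximum, and the committees keep their discretion over the standard care arm.
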